### Measures

An overview of all measurements instruments along with the randomized controlled trial measurement time-points are presented in Table 2.

Demographic characteristics like gender, age, educational level, employment and clinical case history details (duration of alcohol dependence, previous detoxifications and treatments, duration of current abstinence and medication intake) will be collected during the baseline assessment of the TAU.

#### Alcohol Consumption

Weekly alcohol consumption will be assessed using the Alcohol Timeline Follow Back (TLFB) method [40]. For every day of the previous week, patients provide retrospective estimates on the number of standard units alcohol they consumed.

#### Alcohol Dependence

The type and severity of alcohol dependence will be assessed by using the Diagnostic and Statistical Manual of Mental Disorders IV criteria, by means of the Substance Abuse Module (SAM) of the Composite International Diagnostic Interview (CIDI) [41].

#### Craving

The 5-item Obsessive Compulsive Drinking Scale (OCDS) [42] assesses obsessionality and compulsivity related to craving and drinking behavior, and is derived from the original 14-item OCDS scale [43].

#### Health Status

Health status is evaluated using the Maudsley Addiction Profile, Health Symptom Scale (MAP-HSS). The MAP-HSS is a 10-item questionnaire that was adapted from the health scale of the Opiate Treatment Index [44]. Because the MAP-HSS measures only general physical complaints, eight additional alcohol-specific physical complaints were added: hyperventilation, sweating, diarrhoea, heart palpitations, headache, memory problems, sexual problems and epileptic seizures.

#### Depression, Anxiety and Stress

The 21-item Depression Anxiety Stress Scale (DASS-21)[45] is a self-report questionnaire designed to measure depression, anxiety and stress at baseline.

#### Drinking Motives

The baseline drinking motives will be measured using the modified Drinking Motives Questionnaire Revised (mDMQ-R) [46]. The mDMQ-R is a 28-item self-report inventory that assesses the frequency of drinking for each of the original four motives in Cooper’s model [47] with coping motives subdivided into coping-anxiety and coping-depression factors.

#### Self-Efficacy

Using eight items of the Drinking Refusal Self-efficacy Questionnaire (DRSEQ), participants will be asked whether they feel sure they can refuse alcohol on the three subdimensions of self-efficacy: social pressure, emotional relief and opportunism [48].

**Figure 2 figure2:**
[figure not shown]
An example of Approach-Avoidance Training.

**Table 2 table2:** Measurement instruments: purpose, measures and time points.

Purpose and measure^a^		Baseline TAU^b^	Preassessment		Training		Postasssessment		Posttest TAU		Follow-up	
**Cognitive bias assessment**												
	AAT			✓		✓		✓				
**Baseline measures**												
	Demographics	✓										
	MAP-HSS	✓								✓		✓
	DASS	✓								✓		✓
	OCDS	✓								✓		✓
	DMQ-R			✓								
	CIDI	✓										
	Drinking refusal self-efficacy	✓										
**Primary outcome measure**												
	Weekly alcohol consumption	✓		✓		✓		✓		✓		✓
**Secondary outcome measures**					✓							
	CEQ^c^					✓						
	CSQ							✓				

^a^AAT: Approach-Avoidance Task; MAP-HSS: Maudsley Addiction Profile; DASS: Depression Anxiety Stress Scale; OCDS: Obsessive Compulsive Drinking Scale Depression; DMQ-R: Drinking Motives Questionnaire (Revised); CIDI: Composite International Diagnostic Interview; CEQ: Credibilty Expectancy Questionnaire; CSQ: Client Satisfaction Questionnaire.

^b^TAU: treatment as usual.

^c^CEQ will take place in session 2.

#### Credibility of the Intervention

In the second training session intervention, credibility will be assessed using the Credibility and Expectancy Questionnaire (CEQ) [49]. It contains six items and differentiates between a patient’s thoughts and his or her feelings regarding the CBM training.

#### Client Satisfaction

The patient satisfaction regarding the CBM training will be assessed using the Client Satisfaction Questionnaire (CSQ) [50]. It contains 8 items and answers are given on a 4-point scale.

#### Approach-Avoidance Tendencies

Approach-avoidance tendencies are assessed with the AAT pre- and posttraining [23]. The tests consist of 172 trials; 12 practice trials (gray squared pictures) and 160 assessment trials, the latter subdivided into four blocks of trials. Participants randomly receive either set A or set B during assessment. Each set consists of 40 pictures (20 depicting alcoholic beverages and 20 soft drinks) and those are presented 4 times: 2 formats (tilted to the left or right) x 2 repetitions. Alcoholic beverages and soft drink pictures are presented equally often in both formats.

### Primary and Secondary Outcome Measures

The primary outcome measure for this study will be *the proportion of patients reporting alcohol consumption below low-risk drinking limits* (<22 standard units/week for men and <15 for women) [29], since achieving safe drinking is the primary aim of alcohol addiction care. This will be assessed using the TLFB method [40]. As it was not feasible to verify whether all participants met this threshold at the start of treatment and with the knowledge that a previous trial with a similar target group showed that enrolled participants only very rarely report below-threshold consumption levels at baseline [35]-, we allowed all patients to enroll in the study. If necessary, corrections will be made in the analyses.

Secondary outcome measures include changes in approach bias measured by an AAT in the preassessment and postassessment. An AAT bias index is calculated as the difference between the median reaction time scores for pushing pictures of one category (alcoholic beverages or soft drinks) and the median reaction time score for pulling pictures of that category. Median scores are used to minimize the influence of outliers. Positive scores indicate approach tendencies whereas negative scores indicate avoidance tendencies. Furthermore, it is investigated whether the added effect on treatment outcome is mediated by the amount of change in approach bias and who benefits most from training by identifying patient characteristics that moderate the outcome of the training. Other secondary outcome measures are general health condition, depression, anxiety and stress, intervention credibility and patient satisfaction.

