### Aims and Hypotheses

The aim of the current study is to investigate the effectiveness of online CBM Alcohol Avoidance Training as an adjunct to TAU in an outpatient treatment setting. Patients receive eight sessions of either the active or placebo version of the CBM Alcohol Avoidance Training during their TAU. The primary goal is to test the effects of this adjunct CBM on alcohol use immediately after finishing the intervention and three and six months later, by looking at the changes in the level of alcohol consumption over a week. The primary outcome measure is the percentage of the patients reaching the low-risk drinking level, defined as <22 standard units/week for men and <15 for women [29]. It is expected that more patients in the experimental condition will reach low-risk drinking level. Furthermore, it is hypothesized that the CBM intervention decreases or reverses the approach bias, and these changes are expected to mediate the effects on alcohol use [23]. An improvement in health status and a decrease in depression, anxiety and stress for patients in the training condition, compared to the placebo condition, are expected as secondary outcomes. To investigate who benefits most from the training, possible moderators will be examined. Automatic impulses may be controlled by cognitive capacity available to inhibit these impulses. Refusal self-efficacy is considered such a cognitive resource. Following this assumption, CBM interventions can yield benefits, especially for those with a relatively weak cognitive control over their impulses to drink [12,30-32]. In line with the predictions from dual process models and prior CBM trials [12], it is expected that for patients with a low baseline self-efficacy, the additional effect of the Alcohol Avoidance Training will be stronger. Similarly, time-varying self-efficacy is expected to partially mediate the CBM effect as repeated experiences of successful coping due to stronger avoidance responses will enhance refusal self-efficacy. Patients’ adherence and perceptions of treatment acceptability, and credibility will also be examined.

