### Participants and Procedure

The study population consists of patients aged 18 years or older with a primary alcohol problem, who are currently following TAU at Tactus Addiction Treatment Institute in the Netherlands. One general inclusion criterion is accessibility and ability to use the Internet, since patients will need to access CBM-training online. Two exclusion criteria apply for the TAU: (1) serious psychiatric illness with a risk to decompensate while decreasing alcohol consumption; and (2) the possibility of severe physical illness as a consequence of decreased alcohol consumption. There are no additional criteria for participation in this study.

Patients for the training are recruited by therapists at Tactus Addiction Treatment Institute. After the regular intake procedure, including baseline questionnaires, the TAU starts. Before the patient reaches the goal-setting assignment, the therapist will inform the patient about the CBM training and provide the patient with further information about the study. If the patient wants to participate, an informed consent form will be provided to patients by the therapist. After signing the form, the patient receives login credentials for the CBM training from the researcher.

After finishing registration, the patient is randomly assigned to the Alcohol Avoidance Training or to the placebo training, and receives an email with a link to the CBM training website. After logging in, the patient receives instructions about the training. At the start of each session, the patient is asked to complete the additional questionnaires for the purpose of this study, consisting of self-reported weekly alcohol consumption and desire for drinking. Each of the eight training session takes about 10-15 min. The first training session is preceded by an (online) preassessment and the final training session is followed by an (online) postassessment. Three and six months after the postassessment, each patient will receive online follow-up questionnaires. In case of nonresponse, the patient will be reminded by email or phone to complete the questionnaire.

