### Randomization

Patients will be automatically assigned to one of the two conditions (Alcohol Avoidance Training or placebo training, as described in the Intervention section) with an equal likelihood, using the method of minimization [51] in order to balance for type of TAU (online vs face-to-face). The randomization will be computer-generated without any involvement by the investigators. Patients will be randomly allocated to the condition to which the fewest participants of that type of treatment have so far been assigned.

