### Sample Size Calculation

An a priori statistical power analysis (G-power) was conducted to determine the necessary number of participants. The primary outcome measure is a reduction in alcohol consumption. To obtain an estimate of the effect size to be expected, studies describing previous Alcohol Avoidance Training interventions were inspected [21,23]. In both these studies, a relative increase of 20% was observed in effectiveness of TAU + CBM as compared to TAU. The proportion of patients reaching long-term abstinence increased by 13% from 41%-54% [23]. Although in these studies a different dependent measure was used (prolonged abstinence from alcohol), we assume a similar increase in success rate of +13 percentage points as effect size. It has been shown that the Web-based treatment resulted in a 68% success rate (ie, reaching the low-risk drinking criterion) [52]. When extrapolating that to this study, a +13 percentage points additional effect of the Alcohol Avoidance Training is predicted to result in 81% achieving the safe drinking criterion (beta>.80; alpha (one-tailed) <.05). Based on these parameters, 152 patients are needed within a condition to show the hypothesized effects using a Fisher’s exact test for proportions in two independent samples.

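### The plan leaves open whether and how the primary analysis allows for baseline drinking; weekly consumption at TAU baseline should be a fixed covariate

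*Protocol article*

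**What the plan says.** Aims and Hypotheses gives the primary outcome as the "percentage of the patients reaching the low-risk drinking level". Primary and Secondary Outcome Measures defines it as weekly consumption under 22 standard units for men and under 15 for women, without reference to the starting level. That section says it was not feasible to check every participant against the threshold at the start. It reports that a previous trial in a similar group very rarely saw below-threshold consumption at baseline, and concludes: "we allowed all patients to enroll in the study. If necessary, corrections will be made in the analyses". Participants and Procedure sets no consumption criterion.

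Statistical Analyses names a logistic regression comparing the two conditions and lists no covariate. Baseline confounders are to be controlled for only if that proves necessary. The one screen described is a set of ANOVAs and chi-squared tests at baseline, whose non-significance is to show that randomisation worked. Allocation is "with an equal likelihood, using the method of minimization", and the only balancing factor is type of TAU. Table 2 has weekly alcohol consumption recorded at TAU baseline and again at preassessment.

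**The concern.** Neither conditional statement says what would trigger a correction, what form it would take or in which patients it would apply. Leaving out patients already below the limit, adding a covariate and redefining success are all compatible with the text. They estimate different quantities and can give different primary results. A choice made once outcomes are visible weakens the claim to a pre-specified test.

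Baseline significance tests are a poor way to choose covariates. A variable earns its place by predicting the outcome, whether or not the arms happen to differ on it. Starting consumption is a likely strong predictor of being under a consumption limit later, and minimisation does not balance it.

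Patients already under the limit have little room to show a benefit, so they may also dilute the difference between arms.

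**Working it through.** **Inputs from Sample Size Calculation.** Control success: "Web-based treatment resulted in a 68% success rate". The active arm "is predicted to result in 81% achieving the safe drinking criterion". Error rates: "beta>.80; alpha (one-tailed) <.05", where beta is read as power. Size: "152 patients are needed within a condition to show the hypothesized effects", by Fisher's exact test.

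**Step 1: reproduce the plan's figure.** Exact power is the sum of Bin(x_C; n, 0.68) × Bin(x_E; n, 0.81) over all outcomes whose one-sided Fisher p-value is at most 0.05. This gives 0.7999 at n = 151 and 0.803 at n = 152, so 152 per arm is reproduced.

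**Step 2: dilution.** Let f be the share already below the limit and q the probability that they are below it at the outcome assessment, equal in both arms. Assume 68% and 81% apply only to the remaining patients. Then

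p_C = f·q + (1 − f)·0.68

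p_E = f·q + (1 − f)·0.81

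difference = (1 − f)·0.13

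For f = 0.05 and q = 0.9: p_C = 0.045 + 0.646 = 0.691, p_E = 0.045 + 0.7695 = 0.8145, difference = 0.1235.

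One-tailed Fisher power at 152 per arm:

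| f (assumed) | Difference, points | Power, q = 0.9 | Power, q = 1 |
|---|---|---|---|
| 0 | 13.0 | 0.803 | 0.803 |
| 2% | 12.7 | 0.791 | 0.793 |
| 5% | 12.4 | 0.772 | 0.777 |
| 10% | 11.7 | 0.737 | 0.749 |
| 20% | 10.4 | 0.661 | 0.687 |
| 30% | 9.1 | 0.574 | 0.617 |

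With q = 0.9, the loss is 0.803 − 0.791 = 0.012 at 2% and 0.803 − 0.772 = 0.031 at 5%. Every f and q here is an assumption.

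**Step 3: what a fixed covariate gains.** Logistic regression was simulated at 152 per arm (4000 runs, one-sided 5% Wald test), with overall success rates held at 68% and 81% and a standardised baseline covariate of assumed strength. This is a different test from Step 2, so the two sets of power figures should not be compared directly.

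| Log-odds per SD of baseline (absolute value) | Unadjusted power | Adjusted power |
|---|---|---|
| 0 | 0.83 | 0.83 |
| 0.5 | 0.84 | 0.85 |
| 1.0 | 0.84 | 0.88 |
| 1.5 | 0.83 | 0.92 |

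Simulated type I error was 0.048 to 0.060 across both models.

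**Step 4: what analyst freedom costs.** With no treatment effect, assume success in 95% of patients already below the limit and 68% of the others (4000 runs). Three analyses were considered: unadjusted, adjusted for being below the limit, and excluding those patients. Each one, fixed in advance, had one-sided type I error between 0.041 and 0.049. Always taking the most favourable gave 0.053, 0.058, 0.068 and 0.061 at shares of 5%, 10%, 20% and 30%. This is a worst case.

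**The case against.** The case for leaving the text alone has real weight.

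- **Size of the share.** The only indication in the article is that such patients are very rare. Read as 2-5%, that costs about 1 to 3 points of power. A reader might infer from the lower rows of the dilution table that the trial is seriously underpowered, but nothing in the article supports 20% or 30%.
- **Possible double counting.** The 68% is given as the success rate of the Web-based treatment, with no statement that below-limit patients were excluded. If it is a whole-sample rate, and the 13 points likewise, dilution is already included and power stays at 0.80.
- **Timing.** A reader might infer that in the intensive version patients are randomised after sessions 1-5, with drinking already reduced. The article says only: "Before the patient reaches the goal-setting assignment, the therapist will inform the patient about the CBM training". Consent, registration and randomisation follow at no stated session. It is the start of training that is tied to the behavioural-change part, and the brief version has no sessions 2-5. A higher share below the limit by then is possible but not shown.
- **Bias.** A reader might infer that below-limit patients bias the comparison. Randomisation balances them in expectation, and an unadjusted logistic test is valid. Nor are they automatic successes, since they must still report below-limit drinking later.
- **Condensed article.** A separate analysis plan may name the covariates. But this article does more than stay silent: it states a conditional rule in two places, and the rule as stated is open-ended.

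The first four points limit the size of the problem. None of them supplies a rule for when or how to correct.

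**Conclusion.** The point holds as a should-fix. The primary model is conditional in two sections with no stated rule, and a likely strong predictor may be left out although Table 2 shows it is collected. That conclusion needs no assumed share.

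The numerical effect is modest. Power falls from 0.80 to 0.79-0.77 if 2-5% are already below the limit, and to 0.74 at 10%. These figures rest on 90% of them staying below in both arms and on 68% and 81% applying only to the others. The worst-case type I error from free choice was 0.068 against a nominal 0.05. Adjustment gains from nothing to about 9 points of power, depending on how strongly baseline drinking predicts the outcome, which the article does not say.

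It would be wrong to conclude that adjustment undoes dilution: it regains precision but leaves the smaller absolute difference as it is.

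**What to change.** Replace both conditional statements, in Primary and Secondary Outcome Measures and in Statistical Analyses, with a fixed rule:

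- The primary logistic model always includes weekly consumption at TAU baseline, whatever the baseline tests show.
- The TAU-baseline value is used for every patient, with missing values covered by the multiple imputation already planned. It is taken at intake, before randomisation. Preassessment comes after randomisation, and switching between the two according to whether a patient logged in would let behaviour after randomisation decide the covariate's source.
- A supportive analysis is pre-specified in patients at or above the sex-specific limit at TAU baseline (22 units for men, 15 for women). It addresses dilution, which the covariate does not.

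The change should be dated before unblinding. It needs no new data and leaves 152 per arm unchanged. The cost is one extra step: the adjusted odds ratio is conditional on baseline consumption, so a standardised risk difference has to be reported for comparison with the planned 13 points. One limit remains: patients who fall below the limit between intake and the first training session are not identified by the TAU-baseline value.

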### Randomization

Patients will be automatically assigned to one of the two conditions (Alcohol Avoidance Training or placebo training, as described in the Intervention section) with an equal likelihood, using the method of minimization [51] in order to balance for type of TAU (online vs face-to-face). The randomization will be computer-generated without any involvement by the investigators. Patients will be randomly allocated to the condition to which the fewest participants of that type of treatment have so far been assigned.

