### Interventions

#### Treatment as Usual

TAU in this outpatient treatment setting is based on principles of CBT [33] and motivational interviewing [34]. The specific form of the TAU is tailored to the individual needs of the patient, in terms of treatment modality (Web-based or face-to-face) and intensity (brief 5-week version or intensive 3-month version). Study participants, therefore, receive an individualized version of treatment, as is common in regular real-world treatment settings. However, the basic ingredients for all versions are identical: daily registration, the analysis of the functions of the patients’ drinking behavior, behavioral change components, and motivational interviewing. Table 1 provides an overview of the main treatment ingredients. Sessions in face-to-face and Web-based treatment are identical. The only difference is that the contact with the therapist is synchronous in face-to-face treatment, and asynchronous via the Internet in the Web-based treatment [35]. The intensive version of the treatment takes approximately three months with (online or face-to-face) sessions once or twice a week and daily self-reporting of alcohol intake during the whole program. This treatment consists of two parts: a first part focusing on the analysis of the patients’ drinking habits, and a second part starting with the goal setting assignment, followed by sessions geared towards helping the patient reach the set goals and desired behavioral change. The brief 5-week version of the treatment focuses solely on behavioral change (part 2) and is intended for patients who already gained insight into their drinking habits when starting with treatment.

As we are interested in the effectiveness of online CBM Alcohol Avoidance Training as an adjunct to TAU, we do not differentiate between these four treatment “subgroups.” Due to the randomization, the experimental and control group are expected to be balanced concerning treatment modality and intensity.

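### TAU intensity is left to chance in the allocation and to a conditional rule in the analysis; prespecifying it as a covariate is a cheap, small gain in precision

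*Protocol article*

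**What the plan says.** Three sections of the protocol article bear on this.

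- **Randomization.** Patients are allocated "using the method of minimization [51] in order to balance for type of TAU (online vs face-to-face". Each goes "to the condition to which the fewest participants of that type of treatment have so far been assigned". Modality is the only factor in the rule.
- **Treatment as Usual.** TAU varies by modality and by "intensity (brief 5-week version or intensive 3-month version". Of modality the section says: "Sessions in face-to-face and Web-based treatment are identical"; only the timing of therapist contact differs. Of intensity it says: "The brief 5-week version of the treatment focuses solely on behavioral change (part 2". The brief version is meant for patients who already understand their drinking habits, and Table 1 omits sessions 2-5 from it. The section then declines to distinguish the four modality-by-intensity groups, on this ground: "Due to the randomization, the experimental and control group are expected to be balanced concerning treatment modality and intensity".
- **Statistical Analyses.** Demographic variables and outcome measures are tested for baseline differences, non-significance is read as successful randomisation, and baseline confounders are controlled for only where needed. Neither intensity nor any other covariate is named.

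**The concern.** The reason for ignoring intensity is an expectation of balance. That expectation is right on average, but the allocation rule acts on modality alone. The analysis offers only a fallback triggered by baseline testing, and intensity is neither a demographic variable nor an outcome measure, so it may never be tested.

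Intensity could plausibly predict the primary outcome. It is chosen to suit the patient, it selects on insight into drinking, and it differs in length and content. If it does predict low-risk drinking, a chance difference between arms moves the estimated effect a little, and an unadjusted model carries variance that a known baseline variable could remove. What is at stake is precision, in a design whose planned test has almost no spare power.

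**Working it through.** **Inputs from the protocol article (Sample Size Calculation).** Success 68% against 81%, one-sided alpha .05, power .80, 152 per arm, Fisher's exact test.

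**Assumptions, not in the documents.** The brief share b is 30-50%. The difference g in success between versions is 10, 20 or 30 points. The training adds 13 points in each version.

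**1. The plan's own figure.** Exact one-sided Fisher power is .7999 at 151 per arm and .8030 at 152. The stated 152 reproduces, with almost no slack.

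**2. Chance imbalance in intensity.** SD = sqrt(2b(1-b)/152).

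- b = .3: sqrt(.42/152) = .0526. The 95% range is ±10.3 points, and the chance of exceeding 10 points is 6%.
- b = .5: sqrt(.50/152) = .0574. The 95% range is ±11.2 points, and the chance of exceeding 10 points is 8%.

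These treat intensity as unrelated to modality. If the two are correlated, minimising on modality makes the figures slightly smaller.

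**3. Effect on precision.** The standard error of the risk difference is sqrt((.68×.32 + .81×.19)/152) = sqrt(.3715/152) = .0494. The variance due to imbalance is g²×2b(1-b)/152. At b = .5 and g = .20 this is .04×.00329 = .000132, against .0494² = .00244, or 5.4%. The standard error without it is .0494×sqrt(1-.054) = .0481. Approximate power is Φ(.13/SE - 1.645), which is .838 before any adjustment.

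| g | Shift in the 13-point effect at 1.96 SD (b = .3 to .5) | Variance share (b = .5) | SE without it (b = .5) | Approx. power (b = .3; .5) |
|---|---|---|---|---|
| 10 | ±1.0 to 1.1 | 1.3% | .0491 | .841; .842 |
| 20 | ±2.1 to 2.2 | 5.4% | .0481 | .852; .855 |
| 30 | ±3.1 to 3.4 | 12.1% | .0463 | .871; .877 |

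**4. Separating allocation from adjustment.** Simulation used 200,000 trials per scenario, an unadjusted z test and an intensity-stratified Mantel-Haenszel test as a stand-in for the adjusted logistic model.

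- Even split, g = 20: power is .836 (chance, unadjusted), .845 (balanced, unadjusted), .852 (chance, adjusted) and .854 (balanced, adjusted). A second set of 200,000 runs gave .837 (chance, unadjusted), .853 (chance, adjusted) and .852 (balanced, adjusted).
- 30% on the intensive version, g = 20: .837 unadjusted and .850 adjusted, both with chance allocation.
- Even split, g = 10: all four strategies lie between .835 and .839.
- Type I error with chance allocation is .049-.051, adjusted or not. Balancing intensity without adjusting makes the test slightly conservative (.046 at g = 20).

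At g = 20, adjustment alone gains .852 - .836 = 1.6 points at an even split and .850 - .837 = 1.3 points at 30:70. Adding balance to adjustment changes power by between -.001 and +.002.

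**5. The fallback rule.** The protocol sets no threshold for needing adjustment. If intensity were tested at the two-sided 5% level, significance would need an imbalance of about 1.96 SD, that is 10-11 points. Smaller imbalances would pass as successful randomisation.

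**The case against.** The strongest reply is that nothing here is an error. The protocol raises intensity openly, its expectation of balance is correct, and chance imbalance is ordinary random error already covered by the standard error and alpha. That stands: there is no bias, no type I inflation and no change to the 152 per arm.

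A reader might infer that the minimisation factor was wrongly chosen and should be changed. The documents do not support that. Identical session content does not make modality unrelated to outcome: modality is also tailored to the patient, and the 68% planning rate comes from Web-based treatment. Once intensity is in the model, balancing it adds essentially nothing, and recruitment has run since May 2015.

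The difference in treatment content can also be overstated. Training begins with the behavioural-change part of TAU, and Table 1 gives both versions the same sessions 6-10. The omitted sessions come before training, so intensity is mainly treatment history and patient type. It may still be prognostic, but the documents give no success rate by version and no brief/intensive split.

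Lastly, covariates are often named in an analysis plan that is not shown. That limits the point but does not remove it, because the protocol itself states a conditional rule resting on baseline significance tests, and that rule is the weaker method.

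**Conclusion.** The point holds as a cheap improvement. The protocol relies on balance in intensity, secures balance in modality only, and leaves intensity to a conditional adjustment rule. The cost is lost precision: about 1-2 points of power if success differs by 20 points between versions, about 4 at 30 points, and none visible at 10. These figures rest on the assumed 30-50% brief share and the assumed differences between versions. That intensity predicts low-risk drinking is plausible from how patients are assigned to the versions, but the documents do not quantify it. The stronger inference, that the primary comparison is biased or invalid because intensity was not minimised, is not supported.

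**What to change.** In Statistical Analyses, replace the conditional rule for the primary model with a statement such as: the primary logistic regression includes TAU modality (the minimisation factor) and TAU intensity (brief or intensive) as fixed covariates, whatever the baseline comparisons show. Use the version assigned before goal setting, when patients are approached, so that the covariate is a baseline variable. Because the adjusted odds ratio is conditional on these covariates, also report a standardised risk difference for comparison with the planned 13 points. Leave the minimisation as it is.

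The cost is one or two sentences and no extra patients. The TAU version must be extracted for every participant, since neither Measures nor Table 2 lists it as a collected variable. The gain is negligible if the two versions have similar success rates.
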